**Figure 2 F2:**
[figure not shown]
**Flow chart of the CILT study**. Derived from an optimal two-stage design for a phase II clinical trial with the following parameters: *p*_0 _= 0.8, *p*_1 _= 0.95, error probability *α *= 0.05, and error probability *β *= 0.2. Abbr.: *n*, number of patients; *r*, maximum number of responders at which *H*_0 _will not be rejected; *H*_1_, alternative hypothesis.

### Adverse events

All adverse events (AE) are recorded. Events related to the initial diagnosis for liver transplantation, to the transplantation procedure itself, or problems associated with routine procedures after transplantation, i.e. liver biopsy, are not to be noted as AE or serious adverse event (SAE) unless the investigator deems the events to be a cause of the study drug. All SAE potentially associated with the application of study medication must be documented and the sponsor has to be informed by the principal investigator within 24 hours. The sponsor will notify all concerned investigators, the Ethics Committee, and competent authority of findings that could adversely affect the health of subjects. AE will be analysed in an interim analysis and at termination of the trial.

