### Study rationale

Generally, avoidance of CNIs improves kidney function and does not result in higher rate of rejection when an adequate level of immunosuppression is maintained, e. g. by use of non-nephrotoxic immunosuppressive agents such as mTOR-inhibitors and mycophenolate, and/or concomitant interleukin-2 receptor blockade by induction with anti-CD25 antibodies [9-17,23,24]. However, non of the mentioned studies investigated the effect of a CNI-free *de-novo *regimen in patients that underwent liver transplantation.

Based on the aforementioned clinical data this study protocol is designed to show primarily the safety of CNI-free *de-novo *immunosuppression with basiliximab, everolimus, EC-MPS, and corticosteroids in patients after OLT with impaired pretransplant kidney function. To determine whether this regimen has sufficient safety and efficacy to warrant more extensive development and to obtain preliminary data for sample size estimation and planning of a phase III clinical trial this phase II pilot study is designed as a prospective, non-randomized, open-label study. If the CNI-free *de-novo *immunosuppressive regimen gives adequate immunosuppressive protection and is safe with regards to toxicity, a phase III clinical trial will be conducted.

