### Objectives and endpoints

The primary objective of this pilot study is to evaluate the safety and to investigate the preliminary efficacy of a CNI-free immunosuppressive *de-novo *regimen in patients with impaired renal function undergoing liver transplantation. The primary endpoint was thus defined as the incidence of biopsy proven steroid resistant acute rejection(s) within the first 30 days.

Secondary objectives of the trial are the assessment of adverse reactions and renal function under the proposed study regimen. Secondary endpoints will be evaluated after in one interim analysis and after the end of the follow-up period, i. e., one year, and include mortality, the incidence of infection, treatment failure (defined as re-introduction of CNI), wound-healing disturbances, hepatic artery stenoses, and hemato-lymphatic side effects. Furthermore kidney damage will be assessed by the incidence and length of renal replacement therapy and the estimation of renal function using the Modification of Diet in Renal Disease (MDRD) formula. Finally liver allograft function will assessed by measurement of liver enzymes, bile excretion, and coagulation assays.

All end-points will be compared to reference values of CNI based immunosuppression obtained from a meta-analysis [25].

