### Quality assurance

The study is performed according to the principles of the ICH-GCP guidelines and the ethical principles according to the current revision of the Declaration of Helsinki and local legal and regulatory requirements.

The trial is monitored by a contract research organization according to standard operation procedures (SOP) that are based on ICH-GCP guidelines. An independent safety board monitors closely the proper conduct of the trial and all SAE reports to ensure the safety of the subjects during the course of the study.

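### Adverse event recording depends on an open-label causality opinion for transplant-related events, which conflicts with the rule that all adverse events are recorded and under-counts adverse event incidence

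*Protocol article*

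**What the plan says.** The Adverse events section of the protocol article contains three statements that bear on what enters the safety record.

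- The general rule: "All adverse events (AE) are recorded".
- The exclusion covers "Events related to the initial diagnosis for liver transplantation, to the transplantation procedure itself, or problems associated with routine procedures after transplantation", with liver biopsy as the example given. The instruction for all of these is that they "are not to be noted as AE or serious adverse event (SAE) unless the investigator deems the events to be a cause"; the sentence then ends by naming the study drug. As printed, the condition reverses cause and effect; presumably it means events caused by the drug.
- The serious event duty: "All SAE potentially associated with the application of study medication must be documented", with notice to the sponsor within 24 hours.

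The same section says that adverse events are analysed at the interim and at the end of the trial. The abstract (Methods/Design) lists adverse event incidence among the secondary endpoints. Objectives and endpoints names further safety endpoints, including mortality, infection and "wound-healing disturbances, hepatic artery stenoses, and hemato-lymphatic side effects". Under Quality assurance, "An independent safety board monitors closely the proper conduct of the trial and all SAE reports". Study rationale says that the trial is "designed as a prospective, non-randomized, open-label study".

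**The concern.** Causality is normally an attribute of a recorded event. Here, for three broad classes, it is the condition for recording the event at all. Every participant has just had a liver transplant, so much of what happens early on could be placed in one of those classes. The person making the judgement knows the treatment, and there is no concurrent control group to show how often such events occur without the regimen.

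Evaluating safety is part of the primary objective. If the counts are filtered by attribution before analysis, the regimen looks better tolerated than it was. The safety board also sees fewer serious events than occurred, and the planned phase III trial inherits rates that are too low.

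**Working it through.** The plan gives no figure for this point, so the check compares the passages.

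**Step 1: where the two rules differ.** Applying the general rule and the exclusion to each kind of event gives:

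| Event | Attributed to study drug? | Recorded under the general rule | Recorded under the exclusion |
|---|---|---|---|
| Outside the three classes | Either | Yes | Yes |
| Inside a class | Yes | Yes | Yes |
| Inside a class | No, or undecided | Yes | **No** |

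The rules disagree in the last row. A site cannot follow both there.

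**Step 2: direction.** Let N be the number of events that occur and E the number inside a class and not attributed to the drug. The record then holds R = N − E. Since E cannot be negative, R ≤ N. The rule can lower a count but never raise it, and undecided cases drop out by default.

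**Step 3: which results use R.** Three uses follow directly from the text:

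- adverse event incidence, a secondary endpoint in the abstract;
- the interim and final adverse event analyses;
- the serious event reports reviewed by the safety board, because an event not noted as serious does not reach the board by that route.

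**Step 4: thresholds within the section.** The exclusion is lifted when the investigator deems the drug responsible. The serious event sentence asks only for a potential association. A serious, procedure-related event that might be drug-related, but is not deemed so, must be documented under one sentence and is not noted under the other.

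**Step 5: the endpoints named in Objectives and endpoints.** Wound-healing disturbances, hepatic artery stenoses and infections can readily be called related to the operation. Table 2 has rows for rejection, eGFR, laboratory values and ultrasound, but none for wound healing or infection. Adverse events is the one row that would evidently take them. The article does not say that these endpoints come from the adverse event record, nor that they come from anywhere else. The under-count is therefore conditional for them.

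**Step 6: what is untouched.** Rejection has its own rows in Table 2, and steroid resistance needs histological evidence. The two-stage rule counts only patients without steroid-resistant rejection. Neither depends on adverse event labelling. Nothing shows an effect on mortality, renal replacement therapy, eGFR or re-introduction of CNI.

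**The case against.** The fairest defence is that the section states a general rule followed by a definitional carve-out, so there is no contradiction. Expected surgical events are set aside to keep the record readable, and anything blamed on the drug is kept. That reading is possible, although the article does not word the first sentence as subject to exceptions. It also leaves the main point standing: with a carve-out, recording still depends on attribution, and adverse event incidence is still under-counted.

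Other parts of the defence hold, and they limit the point. A reader might infer the following, which the article does not support:

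- **That the rule suppresses the wound-healing, arterial and infection endpoints.** They are listed as endpoints in their own right and may be collected whatever their adverse event label. The missing rows in Table 2 may reflect case report form detail that an article leaves out.
- **That the plan suspects this regimen of causing those events.** The section on the investigational products reports arterial thrombosis and wound-healing problems in a sirolimus trial and says that they were not seen in everolimus trials. It does delay everolimus for safety reasons.
- **That serious events are documented only if drug-related.** The sentence does not say only. It may describe the expedited reporting duty, with other serious events covered by the general rule. The filter on what the board sees is then the exclusion alone.
- **That single-case causality assessment has no value without a control group.** Timing and clinical features can inform it. The objection is to using it as a gate to the record.

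**Conclusion.** The point holds in limited form. As written, the section makes adverse and serious adverse event recording depend on an open-label causality opinion for three classes of event, in conflict with its own opening sentence. This under-counts adverse event incidence and the adverse event analyses, and it narrows the safety board's input. For wound-healing disturbances, hepatic artery stenoses and infections it is a risk that rests on one assumption: that they are drawn from the adverse event record.

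The bias favours the regimen, but its size cannot be stated. A reader might want to set a shortfall against the non-inferiority margin of 0.1. That would need the true event rates and the share attributed to the drug, and the article gives neither. The margin applies only where appropriate, and every analysis other than the primary one is exploratory. The article also does not show how the reference meta-analysis counted events. The confirmatory conclusion on steroid-resistant rejection is unaffected. The change should be made because a stated rule distorts a safety result and is easy to correct.

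**What to change.** Reconcile the Adverse events section with the secondary endpoints in the abstract, with Objectives and endpoints, and with Quality assurance:

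1. Replace the exclusion with a rule that all adverse and serious adverse events through month 12 are recorded regardless of suspected cause.
2. Record relationship to study drug, to the operation and to the underlying disease as attributes of each event. Use causality for expedited reporting, and correct the reversed cause-and-effect wording.
3. Word the serious event sentence so that documentation covers all serious events and the 24-hour duty is a separate statement.
4. State that wound-healing disturbances, hepatic artery stenoses, infections and the other named endpoint events are captured regardless of attribution, and name their data source.

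The cost is a wording change and modest extra data entry for at most 29 patients. Tabulating events by attributed cause would still let a reader separate expected surgical events from the rest. If events have already been left out under the present rule, they would need to be recovered from source records, or the limitation stated in the report.

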### Quality assurance

The study is performed according to the principles of the ICH-GCP guidelines and the ethical principles according to the current revision of the Declaration of Helsinki and local legal and regulatory requirements.

The trial is monitored by a contract research organization according to standard operation procedures (SOP) that are based on ICH-GCP guidelines. An independent safety board monitors closely the proper conduct of the trial and all SAE reports to ensure the safety of the subjects during the course of the study.

### Statistical analysis plan

The confirmatory analysis will be performed for the per-protocol population. All statistical analyses will be performed with a type I error *α *= 0.05 and, where appropriate, a non-inferiority margin of *δ *= -0.1 will be assumed.

All rates will be tested in an approximate one sample design test for non-inferiority [27] against reference values obtained from a pooled meta-analysis of trials with immunosuppressive regimen based on CNI [25].

Confidence intervals will be calculated by the method of Agresti and Coull [28]. The only confirmatory analysis will concern the primary endpoint; all other analyses will be exploratory.

Continuous secondary end-points will be compared to reference values with student's T test unless there is considerable evidence for a non-parametric distribution. Event-time data, i. e., time to acute rejection, patient, and graft survival will be estimated by the Kaplan-Meier method.

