**Methods/Design:**

A prospective therapeutic exploratory, non-placebo controlled, two stage monocenter trial in a total of 29 liver transplant patients was designed to assess the safety and efficacy of *de-novo *CNI-free immunosuppression with basiliximab, mycophenolate sodium, prednisolone and everolimus. The primary endpoint is the rate of steroid resistant rejections. Secondary endpoints are the incidence of acute rejection, kidney function (assessed by incidence and duration of renal replacement therapy, incidence of chronic renal failure, and measurement glomerular filtration rate), liver allograft function (assessed by measurement of AST, ALT, total bilirubin, AP, GGT), treatment failure, (i. e., re-introduction of CNI), incidence of adverse events, and mortality up to one year after OLT.

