### Sample size calculation

The sample size calculation is based on the rate of steroid resistant rejection after OLT. According to the pooled estimate of a Cochrane meta-analysis the incidence of steroid resistant rejection in patients with a CNI based immunosuppressive regimen may be inferred as 12.61% with a 95%-confidence interval of [6.36, 18.65] (estimated by bootstrap methods) [25]. To minimize the sample size for this therapeutic exploratory trial the study is designed as a non-controlled, prospective, two-stage study. In this two stage design [26] superiority of the safety or efficacy rate to the required minimum or "uninteresting" rate *p*_0 _will be tested in stage I. If the treatment is inferior to *p*_0 _the trial will be halted and no further patients enrolled, whereas if the treatment is superior to *p*_0 _stage II will be entered. In stage II the rate will be compared to the actual target rate *p*_1_. For the present trial *p*_0 _and *p*_1 _have been fixed at 0.8 and 0.95 respectively. With error probability *α *= 0.05 and power *β *= 0.2 the required sample sizes for stage I and II are *n*_0 _= 9 and *n*_1 _= 20 respectively. The maximum success rates that corroborate inferiority of the regimen to the fixed rates *p*_0 _and *p*_1 _have been calculated as *r*_0 _= 7 and *r*_0 _+ *r*_1 _= 26, meaning that if more than 7 patients in stage I and 26 patients in stage II do not experience a steroid resistant rejection the true response is at least the target level *p*_1 _(see Figure 2).

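### The only confirmatory test rests on the per-protocol population, which in a single-arm trial can favour the regimen and, if exclusions are not replaced, voids the fixed 9 and 29 patient boundaries

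*Protocol article*

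**What the plan says.** The Statistical analysis plan section fixes the analysis set: "The confirmatory analysis will be performed for the per-protocol population". It also limits confirmatory inference to one endpoint: "The only confirmatory analysis will concern the primary endpoint; all other analyses will be exploratory". It names no all-treated analysis beside the per-protocol one.

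Objectives and endpoints defines the primary endpoint as biopsy-proven steroid-resistant acute rejection in the first 30 days. Re-introduction of CNI is called treatment failure and is a secondary endpoint only.

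The Abstract plans a "two stage monocenter trial in a total of 29 liver transplant patients". In Sample size calculation the uninteresting and target success rates "have been fixed at 0.8 and 0.95 respectively", with 9 patients in stage I and 20 in stage II. The regimen passes "if more than 7 patients in stage I and 26 patients in stage II do not experience a steroid resistant rejection". The second count is cumulative, because the same section gives the sum of the two boundaries as 26. The article shows neither a replacement rule nor a rule for boundaries at other patient numbers.

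**The concern.** The trial asks whether a CNI-free regimen is safe and effective enough to develop further (Study rationale). Patients who could not be kept on it are part of that answer. A per-protocol set is often preferred in a randomised non-inferiority comparison because non-adherence can dilute a difference between arms. Here there is one arm and a fixed reference rate, so that argument does not apply.

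The article shows a route by which patients may leave after enrolment. Exclusion criterion 7 (Table 1) is partly judged before everolimus starts, and Treatment places that start on day 10 at the earliest, inside the 30-day window. CNI re-introduction is a second possible route.

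Two different things are at stake:
- If the excluded patients have more steroid-resistant rejection than those kept, the test is biased towards success.
- If exclusions are not replaced, boundaries set as absolute counts for exactly 9 and 29 patients no longer have the stated error rates.

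**Working it through.** **Inputs.** From Sample size calculation and Figure 2: p0 = 0.80, p1 = 0.95, alpha = 0.05, beta = 0.20, stage sizes 9 and 20, continue if more than 7 of 9 succeed, positive if more than 26 of 29 succeed. The test is one-sided, since the section describes "superiority of the safety or efficacy rate to the required minimum" rate. Success means no steroid-resistant rejection.

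**Formula.** With X1 ~ Bin(9, p) and X2 ~ Bin(20, p) independent,

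P(pass) = P(X1 = 8) × P(X2 ≥ 19) + P(X1 = 9) × P(X2 ≥ 18).

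**Step 1: reproduce the design.**
- p = 0.80: 0.3020 × 0.0692 + 0.1342 × 0.2061 = 0.0486 (type I error).
- p = 0.95: 0.2985 × 0.7358 + 0.6302 × 0.9245 = 0.802 (power).

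A search over two-stage designs for the smallest expected sample size under p0 returns this same design. The stated numbers are correct for exactly 9 and 29 patients.

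**Step 2: exclusions replaced, but related to the outcome.** Let the true rate in all treated patients be 0.80, and let a fraction f of failures be excluded and replaced so that 9 and 29 are kept. The rate in the analysed set is 0.80 / (0.80 + 0.20 × (1 − f)). The document gives no value for f, so this range is assumed.

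| f | Per-protocol rate | P(pass) |
|---|---|---|
| 0 | 0.800 | 0.049 |
| 10% | 0.80/0.98 = 0.816 | 0.073 |
| 25% | 0.80/0.95 = 0.842 | 0.133 |
| 50% | 0.80/0.90 = 0.889 | 0.342 |

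**Step 3: exclusions not replaced and unrelated to the outcome (assumption).** Losses fall in stage II, and stage I stays at more than 7 of 9.

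| Evaluable | Cut-off kept at >26: alpha / power | At most 2 failures allowed: alpha / power |
|---|---|---|
| 29 | 0.0486 / 0.802 | 0.0486 / 0.802 |
| 28 | 0.0155 / 0.588 | 0.0568 / 0.814 |
| 27 | 0.0024 / 0.250 | 0.0663 / 0.825 |
| 26 | 0 / 0 (27 successes needed) | 0.0773 / 0.835 |

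The last column is not a rule in the article. It is the natural alternative if the count is allowed to move with the number analysed. At 28 patients, neither cut-off gives both alpha ≤ 0.05 and power ≥ 0.80.

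**Step 4: one exclusion in stage I, not replaced.** More than 7 of 8 means 8 of 8. At p = 0.95 the chance of continuing is 0.95^8 = 0.663, against P(X1 ≥ 8) = 0.2985 + 0.6302 = 0.929 with 9 patients. With two exclusions, stage I cannot be passed.

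**The case against.** The strongest reply is that the article does not define per-protocol and shows no replacement rule. It condenses a fuller protocol that may settle both, and 9 and 29 may be meant as evaluable patients. A patient with steroid-resistant rejection who is then given CNI may be counted as a failure before any exclusion. All of this stands. It makes the figures in Steps 2 to 4 conditional, and the absence of those rules from the article is not itself the finding. It does not remove the point, because the choice of set is stated, and replacement would restore the counts without removing the selection.

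The two effects also run in opposite directions. Unreplaced exclusions unrelated to outcome, with cut-offs kept, lower alpha and cost power. That is conservative for a safety screen in an exploratory trial meant to lead to a randomised one. The false-positive rate rises if failures are selectively dropped or if the cut-off moves with the number analysed.

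A reader might infer that per-protocol exclusion is always anti-conservative here because every patient returned to CNI is a hidden failure. The documents do not support that, since CNI re-introduction is a secondary endpoint and not a primary failure. Suppose 10% of patients have steroid-resistant rejection and another 10% switch to CNI without it. Success on the protocol's endpoint is then 0.90 in all treated patients, with pass probability 0.414. Dropping the switchers gives 0.80/0.90 = 0.889 and 0.342, so in that case per-protocol makes passing less likely. The bias favours the regimen only if excluded patients have, or would have had, more steroid-resistant rejection than those kept.

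**Conclusion.** The concern holds in conditional form. Making per-protocol the sole confirmatory set is a poor choice for a single-arm trial with this purpose, and the usual non-inferiority argument for it does not carry over.

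The upward bias assumes that failures are over-represented among exclusions, which is plausible where CNI is re-introduced because of rejection but is not shown. The assumed range puts the false-positive rate at 0.073 to 0.342 instead of 0.049. The loss of operating characteristics assumes at least one unreplaced exclusion. The planned total equals the design total, so there is no slack, and a single such exclusion is enough to miss either the stated alpha or the stated power.

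The article does not support saying that the test is certainly biased or that the boundaries will certainly fail.

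**What to change.** - Define the confirmatory set as all enrolled, transplanted and treated patients in order of enrolment: the first 9, then all 29.
- Count the primary endpoint as already defined, whether or not the patient stayed on the regimen.
- Keep the per-protocol analysis as a sensitivity analysis.
- Add a sensitivity analysis that counts patients with unknown 30-day status as non-successes. Making that the main rule would turn the endpoint into a composite. With at most 2 failures allowed in 29, events unrelated to steroid-resistant rejection could then decide the result, and p0, p1 and power would have to be reconsidered.
- State that if the attained number differs from 9 or 29, the boundary is recomputed exactly for H0: p ≤ 0.80.

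The cost is a change of wording, with no added patients or visits. The reported success rate may be slightly lower.

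### The primary endpoint has two decision rules, an exact two-stage rule and an approximate non-inferiority test, and the protocol article does not say which one decides

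*Protocol article*

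**What the plan says.** The protocol article's Sample size calculation section sets up an optimal two-stage design for the proportion of patients free of steroid-resistant rejection. The uninteresting and target rates "have been fixed at 0.8 and 0.95 respectively". The sizes are 9 and 20, and the cut-offs are explained as "meaning that if more than 7 patients in stage I and 26 patients in stage II do not experience a steroid resistant rejection". Since stage II adds only 20 patients, the 26 must be the cumulative count out of 29.

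The same section takes the CNI reference from a meta-analysis: the "incidence of steroid resistant rejection in patients with a CNI based immunosuppressive regimen may be inferred as 12.61" per cent.

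The Statistical analysis plan section does not mention the two-stage rule. It says "All rates will be tested in an approximate one sample design test for non-inferiority", against reference values from that meta-analysis. It gives a margin of -0.1, to be used where it fits, an alpha of 0.05, and a per-protocol population for the confirmatory analysis. It adds: "The only confirmatory analysis will concern the primary endpoint". The Objectives and endpoints section defines the primary endpoint as a 30-day incidence, and says that every endpoint will be compared with the meta-analysis values.

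**The concern.** The primary endpoint is a rate, so it falls under both rules. One tests against a fixed 80%. The other tests against a benchmark derived from the CNI reference. The article does not rank them, and it does not relate 0.80 to the reference minus the margin.

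The operating characteristics quoted for 29 patients were worked out for the two-stage rule. The analysis section attaches the word confirmatory to a passage that describes only the other test, which has no power statement and, as described, makes no allowance for the stage-I stop. If the two verdicts differ, the article does not say whether the regimen has passed, and that verdict is meant to decide whether a phase III trial follows.

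**Working it through.** **Inputs.** From Sample size calculation: p0 = 0.80, p1 = 0.95, continue if more than 7/9, succeed if more than 26/29, reference rejection rate 12.61%. From the Figure 2 caption: "error probability *α *= 0.05, and error probability *β *= 0.2" (the running text calls the second figure power; the caption's reading is used). From Statistical analysis plan: margin -0.1, alpha 0.05, per-protocol set. Assumption: one-sided 0.05, since sidedness is not stated. The variance form of the approximate test is not stated either, so several are tried.

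**Step 1: reproduce the design.** The chance of success at true rate p is the sum over x = 8, 9 of P(X1 = x; 9, p) × P(X2 ≥ 27 − x; 20, p).
- p = 0.80: 0.3020 × 0.0692 + 0.1342 × 0.2061 = 0.0486.
- p = 0.95: 0.2985 × 0.7358 + 0.6302 × 0.9245 = 0.802.

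A search over all designs up to 45 patients returns 7/9 and 26/29 as optimal. The design is correct as printed.

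**Step 2: the null of the second test.** The reference success rate is 1 − 0.1261 = 0.8739. With the margin, the null is 0.8739 − 0.10 = 0.7739. Without it, the null is 0.8739. Neither figure is printed as a null.

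**Step 3: compare verdicts.** Score z = (x/n − null) / √(null(1 − null)/n). Wald z uses x/n in place of the null under the root. Exact p is the single-stage binomial upper tail. The pass mark is z ≥ 1.645 or p ≤ 0.05.

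| Result | Null | Score z | Wald z | Exact p | Second test | Two-stage rule |
|---|---|---|---|---|---|---|
| 26/29 | 0.7739 | 1.58 | 2.17 | 0.080 | passes under Wald only | fails |
| 27/29 | 0.7739 | 2.02 | 3.34 | 0.026 | passes | passes |
| 26/28 | 0.7739 | 1.96 | 3.18 | 0.032 | passes in all three forms | printed cut-off not met |
| 27/29 | 0.8739 | 0.93 | 1.21 | 0.27 | fails in all three forms | passes |

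**Step 4: error rate of the Wald cut-off.** Accepting 26/29 or better after passing stage I has probability 0.2618 × 0.1370 + 0.0996 × 0.3058 = 0.066 at 77.39%. Without the stage-I gate it is 0.080. Under the score or exact form (27/29 or better, after the gate) it is 0.024 at 77.39%.

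**Step 5: is 26/28 only an artefact of a cut-off printed for 29?** Suppose the lost patient is in stage II, so that 19 remain there. A cut-off of at least 26/28 has type I error 0.3020 × 0.0829 + 0.1342 × 0.2369 = 0.057 at p = 0.80, above 0.05. A recomputed cut-off would be 27/28, so 26/28 fails the two-stage rule on that basis too. Power at 0.95 would then be 0.2985 × 0.3774 + 0.6302 × 0.7547 = 0.588.

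**Step 6: sidedness.** At one-sided 0.025 and null 0.7739, 26/28 passes only under Wald (score 1.957 against 1.960; exact 0.032). At 27/29 the score form still passes, while the exact form just fails (0.026).

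**The case against.** The strongest reply is that the two rules need not conflict. With exactly 29 evaluable patients, the margin applied, and a score or exact test at one-sided 0.05, both need 27/29. Only the Wald form lets 26/29 through, and the article does not say that Wald will be used; the cited method may be another. All of that stands. A reader might infer from the differing nulls (80% and 77.39%) that the tests are incompatible, or that the sponsor may pick a verdict at will. The article does not support that: different nulls do not by themselves give different verdicts here, and under Wald with 29 patients at one-sided 0.05 the disagreement is confined to 26/29.

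Four further criticisms are tempting but do not belong to this point:
- The 26/29 cut-off is met 11.7% of the time at a true rate of 80%. For a test whose null is 77.39%, 80% lies in the alternative, so this is not its type I error; the gated figure is 6.6%.
- A regimen equal to CNI reaches 27/29 only 25.9% of the time. That is equally true of the two-stage rule.
- The reference has its own confidence interval. This is uncertainty in a benchmark, not a conflict between rules.
- A margin of -0.1 would point the wrong way for an adverse-event rate. The design codes outcomes as successes, the margin is limited to where it fits, and secondary rates are exploratory.

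The reply does not answer the missing precedence. The confirmatory set is per-protocol, so fewer than 29 evaluable patients is foreseeable, and 26/28 is discordant at one-sided 0.05 whichever form is used. If the margin is held not to apply, 27/29 is discordant in the other direction. A fuller analysis plan might settle the matter, but the article states both rules itself.

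**Conclusion.** The point holds as an unresolved precedence. One confirmatory endpoint has two decision rules, and the stated alpha and power were derived for only one of them. The verdicts agree on the most favourable reading and differ at 26/29 (Wald), 26/28 (per-protocol, margin applied) and 27/29 (margin not applied). These results assume one-sided 0.05 and a null built as the reference success rate with or without the margin. Ignoring the stage-I stop does not by itself inflate error, since the gate lowers the Wald figure from 8.0% to 6.6%; it does mean that the second test's properties are not those quoted.

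Severity is moderate. This is an exploratory single-arm pilot, and its two-stage design is correct.

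**What to change.** 1. In the Statistical analysis plan section, name the exact two-stage rule (stop at 7/9 or fewer; reject a success rate of 0.80 or less with 27/29 or more; one-sided 0.05) as the sole confirmatory test of the primary endpoint.
2. There and in Objectives and endpoints, label the comparison with the CNI reference supportive or exploratory, and use an exact binomial test or interval for it.
3. State how the two-stage rule works when the evaluable number is not 9 or 29. One option is to apply the printed cut-offs to all enrolled and treated patients. Another is to recompute the final cut-off for the attained number at p0 = 0.80. The second option can cost power: losing one stage-II patient takes it from 0.802 to 0.588 at p1.

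The change is to wording only. The sponsor gives up a confirmatory claim of non-inferiority to CNI, for which the 29 patients were not sized.
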